### 3.2. Sample

The sample will include 325 typically developing children and one of their caregivers. To be eligible the children must be aged 8–12 years, have a body mass index (BMI) greater than or equal to the 50^th^ and less than the 95^th^ percentile, and typically sleep <8.5 h per night. Children will be excluded if they have a diagnosis of a major medical condition and/or take medications that impact sleep. Caregivers must be available to put their child to bed on the majority of nights during the study and have smartphone, tablet, or computer access for the duration of the intervention. Table 2 lists the full inclusion and exclusion criteria. Eligibility will be assessed using a screening questionnaire, with the exception for BMI, which will be assessed using measured height and weight at the baseline study visit, and sleep duration, which will be assessed during the run-in phase.

**Table 2 T2:** Inclusion and exclusion criteria for children and caregivers by eligibility assessment phases.

**Screening phase inclusion criteria for children**	**Children aged 8 to 12 years**
	Speak, read, and write in English
	Parental/guardian permission (informed consent) and child assent
Screening phase exclusion criteria for children	A clinically diagnosed chronic disease falling under one or more of the following categories: congenital birth defects, syndromes, or abnormalities; cardiac, hematological, oncological, immunological, pulmonary, renal, rheumatological, or musculoskeletal conditions; endocrine, gastrointestinal, metabolic, sleep, neurodevelopmental, or weight disorders
	Children regularly taking medications related to exclusionary medical conditions or that impact sleep
	Children who will transition to high school during the study
	Children who share a bed
	Children enrolled in another clinical trial
	Have a parent/guardian works, or has a family member who works, for the Division of Gastroenterology, Hepatology and Nutrition at CHOP
Screening phase inclusion criteria for caregivers	Be the parent/guardian of an eligible child enrolled in the main study
	Speak, read, and write in English
	Be available to but the child to bed on the majority of nights
	Have access to a smartphone to install the sleep tracking application for the duration of the study
Baseline study visit inclusion criteria for children	BMI ≥ 50^th^ and <90^th^ percentile for age and sex
Run-in period inclusion criteria for children	Sleep duration ≤ 8.5 hours per night on average

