### 3.5. Outcomes

#### 3.5.1. Primary outcomes

The primary outcomes are nighttime sleep duration (hours per night) on weeknights and fat mass index (kg/m^2^). Sleep duration will be estimated using the sleep tracker. Up to 260 weeknights (Sun-Thurs) and 104 weekend nights (Fri and Sat) of data will be captured per participant. Federal holidays and notable events (e.g., vacations) occurring on weeknights during the school term will be re-coded as weekend nights. Weeknights are the focus since insufficient sleep among children is more prevalent on weeknights.

Total body fat mass will be measured by DXA (Hologic Discovery A; Hologic Inc., Bedford, MA, operating in software version 13.5.3) at baseline, 6-months, and 12-months. Fat mass index (FMI, kg of fat divided by height in meters squared) will be calculated, and age and gender specific FMI Z-scores will be determined using U.S. specific FMI growth charts (Weber et al., 2013).

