#### 3.5.2. Secondary outcomes

Secondary outcomes include sleep timing metrics from the sleep tracker to understand if any changes in sleep timing lead to changes in sleep duration. The sleep timing metrics include sleep onset on weeknights and weekend nights (hours from 00:00), sleep offset on weeknights and weekend nights (hours from 00:00), and sleep midpoint on weeknights and weekend nights (hours from 00:00). “Social jetlag” will be calculated by subtracting the weekend night sleep midpoint from the weeknight sleep midpoint. Social jetlag provides an indication of the discrepancy between internal biological clocks and social requirements and has been linked to cardiometabolic risk (Cespedes Feliciano et al., 2019; Mathew et al., 2020). Sleep quality metrics will also be captured from the sleep tracker on weeknights and weekend nights: sleep efficiency (percentage of time spent asleep during overnight sleep periods), sleep onset latency (time to fall asleep), and wake after sleep onset (time awake during overnight sleep periods).

Secondary outcomes also include sleep disturbance and sleep impairment measured using the Patient-Reported Outcomes Measurement Information System (PROMIS) item bank for pediatric sleep (Forrest et al., 2018). This validated survey generates a sleep disturbance T-score based on items related to sleep onset, sleep continuity and sleep quality in the past week. The survey also generates a sleep-related impairment T-score based on items related to daytime sleepiness, cognition, affect and behavior, and daytime activities in the past week. Higher T-scores indicates poorer sleep quality (Forrest et al., 2018). Participants will complete this survey at baseline and at the end of each month during the intervention and follow-up phases.

Secondary outcomes will also be considered with respect to body composition and size. These include visceral body adipose tissue area (cm^2^), waist circumferences (cm), and BMI (kg/m^2^).

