### 3.6. Power calculation

#### 3.6.1. Aim 1

The primary outcome for Aim 1 is nighttime sleep duration (hours per night) on weeknights (measured daily by the sleep tracker). The “MOST” R package (FactorialPowerPlan) was used to determine the sample size needed to detect a 30 min per night difference in nighttime sleep duration on weeknights (alpha = 0.05; power = 0.8; pretest-posttest correlation of sleep duration = 0.7; and a standard deviation sleep duration = 0.7 h per night). The effect size and parameters were derived from our prior studies. The calculation accounted for detection of main effects plus all possible interactions. The power calculation revealed that a minimum sample size of 41 was needed for Aim 1.

#### 3.6.2. Aim 2

The primary outcome for Aim 2 is fat mass index (kg/m^2^) (measured at baseline, 6-months, and 12-months by DXA). The “MOST” R package (FactorialPowerPlan) was used to determine the sample size needed to detect a 0.25 kg/m^2^ reduction in fat mass index at 6-months and 12-months (alpha = 0.05; power = 0.8; pretest-posttest correlation of fat mass index = 0.9; and a standard deviation for fat mass index = 0.9). The effect size and parameters were derived from our prior studies. The calculation accounted for detection of main effects plus all possible interactions. The power calculation revealed that a minimum sample size of 282 was needed for Aim 2.

#### 3.6.3. Aim 3

The primary outcome for Aim 3 is nighttime sleep duration (hours per night) on weeknights (measured daily by the sleep tracker). It has been observed that male children sleep on average 12 min per night less than female children, and that African American/Black children sleep on average 33 min per night less than non-Latinx White children (Guglielmo et al., 2018; Billings et al., 2021; Min et al., 2021). We will determine if the effectiveness of the optimal component settings for sleep promotion differ by ≥20 min across sociodemographic factors. This calculation revealed that 286 participants are needed to detect a ≥20 min per night difference in the effectiveness of the optimal component settings for sleep duration by higher and lower sociodemographic levels. The calculation was completed in Stata (version 14.2) using the “power repeated” command to compute the sample size. The parameters used for the calculation were: alpha = 0.05, power = 0.8, number of repeated measures = 52, number of groups = 2, error variance = 1.1, and correlation = 0.7.

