### 3.7. Statistical plan

Under the intent to treat principle, we will use all available data and participants under the assumption of missingness at random. No participants will be excluded from the analysis except for the unlikely case of no outcome measurements for a participant. Final models will be adjusted for covariate dependent missingness due to dropout. We will examine sensitivity to the assumptions about the missing data mechanism.

#### 3.7.1. Aim 1

Mixed-effects linear regression models will be used to determine if the intervention components are associated with changes in weeknight sleep duration from baseline. The fixed model components will include indicators for each factor (with effect coding used to identify each component level), time in weeks, and all possible interactions between time and factors. The full model will be reduced to a more parsimonious model by selecting the main effects and interactions achieving a Type I error rate of alpha = 0.05.

#### 3.7.2. Aim 2

Mixed-effects linear regression models will be used to measures changes in fat mass index using the most parsimonious model from Aim 1 (i.e., optimal component settings for sleep promotion).

#### 3.7.3. Aim 3

The most parsimonious model from Aim 1 (i.e., optimal component settings for sleep promotion), will be expanded to determine if effectiveness differs by sociodemographic factors. The fixed model components will include indicators for each component (effect coding to represent the levels of each factor), time in weeks, the sociodemographic factor of interest, interactions between time, component(s), and sociodemographic factor. The sociodemographic factors that will be modeled include sex, race/ethnicity, and neighborhood context (poverty, sound, canopy cover, housing and population density, and street connectivity).

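### The Aim 2 model for FMI change names no age or sex term, so age- and sex-specific growth stays in the residual: a modest, avoidable loss of precision, not a bias

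*Protocol article*

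**What the plan says.** All references are to the protocol article.

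- **Outcome (3.5.1).** FMI in kg/m² is one of the two primary outcomes. The section adds that "age and gender specific FMI Z-scores will be determined using U.S. specific FMI growth charts". These scores have no role in the power calculation or the statistical plan.
- **Population (3.2).** "To be eligible the children must be aged 8–12 years". FMI is measured at baseline, 6 and 12 months.
- **Sizing (3.6.2).** Aim 2 is powered for a 0.25 kg/m² "reduction in fat mass index at 6-months and 12-months", with SD 0.9, pre-post correlation 0.9, alpha 0.05 and power 0.8. The stated minimum is 282.
- **Aim 2 model (3.7.2).** "Mixed-effects linear regression models will be used to measures changes in fat mass index using the most parsimonious model from Aim 1".
- **The model carried over (3.7.1).** "The fixed model components will include indicators for each factor (with effect coding used to identify each component level), time in weeks", plus the interactions of time and factors. Terms are then kept or dropped at alpha 0.05, with weeknight sleep as the outcome.
- **Where sex appears (3.7.3).** Sex is one of the sociodemographic factors by which the Aim 1 model is extended to study sleep under Aim 3. Age is not named in any model.
- **Other covariates (3.7).** "Final models will be adjusted for covariate dependent missingness due to dropout". The covariates are not named.

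**The concern.** A model chosen for sleep is reused for a growth outcome. The protocol itself standardises FMI by age and sex, and follows children of quite different ages for a year. If boys and girls, or 8- and 12-year-olds, differ in how much FMI changes over 12 months, a model without those terms counts the difference as residual variation. The standard errors of the component contrasts are then larger than they need be.

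At stake is efficiency on a co-primary outcome. Both variables are already needed for the BMI percentile and the Z-scores, so the precision could be had without extra data collection.

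**Working it through.** **1. What can reach the residual.** Average growth is common to all children and is taken up by the time term. Differences in FMI level at baseline drop out of change from baseline. What is left is how far change in a given age or sex group departs from the average change.

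**2. The plan's own figure.** For a main effect in a 2⁴ factorial, half the sample is compared with half. The change-score variance is 2 × SD² × (1 − r).

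- Aim 1 (SD 0.7, r 0.7, difference 0.5 h): variance 2 × 0.49 × 0.3 = 0.294, SD 0.542. A two-sided noncentral t with 16 model parameters gives N = 41, as stated in 3.6.1.
- Aim 2 (SD 0.9, r 0.9, difference 0.25): variance 2 × 0.81 × 0.1 = 0.162, SD 0.402. The same method gives N = 84, not 282.
- Residual SD that would yield 282, by the normal approximation N = 4σ²(1.96 + 0.84)²/0.25²: σ ≈ 0.749, variance ≈ 0.561.

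The stated inputs and the stated 282 therefore imply different residual variances, and both are carried forward.

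**3. Share due to sex.** The documents give no sex difference D in 12-month FMI change, so D is assumed. With equal numbers of boys and girls, D contributes variance D²/4. Completers are 325 × 0.9 ≈ 292. The children columns are 292 × share.

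| D (kg/m²) | D²/4 | share of 0.162 | children | share of 0.561 | children |
|---|---|---|---|---|---|
| 0.1 | 0.0025 | 1.5% | 5 | 0.4% | 1 |
| 0.2 | 0.0100 | 6.2% | 18 | 1.8% | 5 |
| 0.3 | 0.0225 | 13.9% | 41 | 4.0% | 12 |
| 0.4 | 0.0400 | 24.7% | 72 | 7.1% | 21 |

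At D = 0.4 the standard error falls by 1 − √(1 − 0.247) ≈ 13% on the first variance and 1 − √(1 − 0.071) ≈ 4% on the second. An age gradient in change would add to this, but the documents give nothing from which to size it.

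**4. Effect on power at 292 completers.**

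- Stated SD and correlation: power for 0.25 kg/m² exceeds 99.9% without adjustment. If sex variation is added on top of 0.162, even D = 1.0 (variance 0.162 + 0.25 = 0.412, SD 0.642) needs N = 210 and leaves power of about 91%.
- Residual SD 0.749: power is Φ(0.25 × √292 / (2 × 0.749) − 1.96) = Φ(0.89) ≈ 81%. Removing 7.1% of the variance gives Φ(2.852/0.964 − 1.96) = Φ(1.00) ≈ 84%.

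**The case against.** The strongest objection is that this is a condensed article without its SAP, that prognostic covariates are commonly left to the SAP, and that the list of fixed effects is not said to be exhaustive. The sentence on missingness even allows unnamed covariates. This has weight, and silence about age and sex alone would be thin ground. But 3.7.2 does more than stay silent: it defines the Aim 2 analysis by reference to a particular model. Section 3.7.3 indicates that sex is outside that model, because sex is among the factors by which it is extended. Adjustment for covariates that predict dropout has a different purpose from modelling growth.

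It is also fair that D is assumed, and that the planning SD and correlation come from prior studies of raw FMI and may already contain growth differences. Adjustment would then be a gain over the plan, not the repair of a shortfall.

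A reader might infer more than the text supports:

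- *That normal growth as a whole becomes error.* Step 1 of the working shows that only age- and sex-specific departures in change do.
- *That the primary scale is open between kg/m² and Z-score.* It is not. Sections 3.5.1, 3.6.2 and 3.7.2 all use FMI itself, and no section calls the Z-score primary.
- *That Aim 2 drives the trial size.* Section 3.6.3 requires 286 for Aim 3, against 282 for Aim 2.
- *That the same flaw is stated for* "waist circumferences (cm), and BMI" *in 3.5.2.* The plan specifies no model for those outcomes.

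**Conclusion.** The point holds as a modest efficiency gain. As written, the Aim 2 model leaves age- and sex-specific differences in FMI change in the residual. The component contrasts remain unbiased, and no stated power shortfall follows.

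For an assumed sex difference in change of 0.1 to 0.4 kg/m² and equal numbers of boys and girls, the recoverable share is 1.5% to 25% of the change variance on the stated SD and correlation. It is about 0.4% to 7% if the stated 282 reflects the true residual variance. The true difference, and any contribution from age, cannot be read from the documents. On neither variance does the omission by itself put the Aim 2 test at risk.

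**What to change.** In 3.7.2, state that the FMI model includes baseline age, sex and their interactions with visit as fixed effects, and that these are exempt from the significance-based reduction carried over from Aim 1. Keep FMI in kg/m² as the primary scale, as already stated and as the 0.25 kg/m² target requires. Give the Z-scores a role by reporting that analysis as supportive.

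The change should be written in before outcome data are examined. It costs a few sentences and a few degrees of freedom, and needs no new data.

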##### 3.5.1.1. Optimization objective

The optimal component settings will have to meet the following criteria: increase average baseline sleep duration on weeknights by ≥30 min for ≥75% of intervention weeks and for ≥50% of follow-up weeks. A 30-min increase in sleep duration has been shown to be feasible in our prior research (Mitchell et al., 2021) and has been shown to improve alertness and emotional regulation (Gruber et al., 2012) and to lower weight gain (Hart et al., 2022).

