
### 1.7. Proof of principle: promoting sleep using a mobile health platform

We have successfully deployed a mobile health platform with an integrated sleep tracker, digital messaging, and a behavioral economic inspired incentive for sleep promotion among typically developing children, aged 9–12y, at the Children's Hospital of Philadelphia (Mitchell et al., 2021). The digital messaging components provided feedback on sleep goal achievement and included general sleep health information (i.e., information about bedtime electronics usage) (Mitchell et al., 2021). The behavioral economic component delivered financial incentives to parents based on child sleep goal achievements (Mitchell et al., 2021). We specifically explored the effectiveness of a gain-framed incentive (i.e., accumulated money if sleep goals were achieved) and a loss-framed incentive (i.e., money deducted from an upfront endowment if sleep goals were not achieved) (Mitchell et al., 2021). Based on Prospect Theory, the loss-framed structure should be more motivational because of loss aversion (Tversky and Kahneman, 1981). Interestingly, compared to the control arm, the loss-framed incentive arm increased sleep duration by an average of 34 min per night and increased the probability of sufficient sleep (≥9 h per night) by an average of 18 percentage points (Mitchell et al., 2021). There was no change in sleep duration in those randomized to the gain-framed incentive. Importantly, qualitative data revealed that barriers to sleep extension were primarily related to competing academic and extracurricular demands, as well as sibling activities and caregiver work schedules (Mitchell et al., 2021). In addition, families reported challenges around creating consistent rules related to electronics usage (Mitchell et al., 2021). Facilitators were also noted for future intervention. Children desired more personalized messaging to target their specific sleep habits, while parents suggested enhancing sleep health messaging content (Mitchell et al., 2021).

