#### 3.3.2. Run-in phase

Children will be asked to maintain their usual sleep patterns for a 2-week period to capture their baseline sleep duration. It is expected that sleep duration may increase upon self-monitoring sleep, so the 2nd week of the run-in phase will define each participant's baseline sleep duration. If sleep duration measured by the sleep tracker is greater than or equal to 8.5 h per night on average during the second run-in week they will be excluded. In addition, if <2 nights of data are provided during the second run-in week, they will be excluded due to poor compliance. Otherwise, they will be randomized to a study condition for the optimization trial.

Additionally, baseline dietary intake will be captured during the 2nd week of run-in phase via three 24-h dietary recalls. A self-reported sleep diary will also be completed during the 2nd week of the run-in phase.

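### The 30-minute optimization mark is a raw rise from the same run-in week used to select short sleepers, so regression to the mean and calendar timing count toward it

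*Protocol article*

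**What the plan says.** Section 3.5.1.1 sets the decision rule for the optimization phase. Settings must "increase average baseline sleep duration on weeknights by ≥30 min for ≥75% of intervention weeks and for ≥50% of follow-up weeks". The rule names no reference condition.

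Section 3.3.2 fixes the baseline: "the 2nd week of the run-in phase will define each participant's baseline sleep duration". The same week decides eligibility, since children whose sleep is "greater than or equal to 8.5 h per night on average during the second run-in week they will be excluded". The data requirement is light: "if <2 nights of data are provided during the second run-in week, they will be excluded due to poor compliance". Week 1 is set aside for a stated reason: "It is expected that sleep duration may increase upon self-monitoring sleep".

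In Table 1 and section 3.3.4, all 16 conditions have a sleep goal, text messages and the tracker. Only the incentive and the performance feedback have an inactive level.

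Section 3.5.1 counts up to 260 weeknights per child, which is 52 × 5 and so covers the full year. Its exception is limited to term time: "Federal holidays and notable events (e.g., vacations) occurring on weeknights during the school term will be re-coded as weekend nights".

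Section 3.7.1 tests effect-coded randomized factors and their interactions with time, and keeps terms at alpha 0.05. Sections 3.7.2 and 3.7.3 equate the reduced model with the optimal settings. Section 3.6.1 powers Aim 1 for a 30-min difference, with "pretest-posttest correlation of sleep duration = 0.7" and an SD of 0.7 h.

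**The concern.** One short, noisy measurement does two jobs. It admits a child only if it is low, and it is then the value from which the rise is measured. When the correlation between baseline and later weeks is below 1, children chosen for a low value will on average be higher later, with no intervention effect. Dropping run-in week 1 deals with reactivity to the tracker. It does not deal with selection on week 2.

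The mark is also a different quantity from the figures around it. In the pilot (section 1.7), "compared to the control arm, the loss-framed incentive arm increased sleep duration by an average of 34 min per night", which is a contrast. The 30 min in the Aim 1 power calculation is a contrast too. The pass mark is an uncontrolled change, and the article does not say how it relates to the section 3.7.1 contrasts.

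The calendar adds to this. Vacations and holidays in term are moved out of the weeknight outcome, but summer-break weeknights stay in. A week can pass or fail because of where the child's summer falls.

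At stake is the purpose stated in section 1.8: to remove or adjust weak components before an expensive evaluation trial. A mark that is partly met by selection can send a package forward on less benefit than the 30 min suggests.

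**Working it through.** **The plan's own figure.** The inputs from section 3.6.1 are a difference of 0.5 h, SD 0.7 h, r 0.7, alpha 0.05 and power 0.8.
- Change-score variance = 2 × SD² × (1 − r) = 2 × 0.49 × 0.3 = 0.294.
- A noncentral F test of one effect-coded factor in a 16-parameter model gives N = 41, the figure stated. The SD and r are thus being read as the plan uses them, and the calculation is for a randomized contrast.

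**Expected rise with no intervention effect.** Let the run-in mean in screened children be normal with mean μ and SD 0.7 h, cut off at 8.5 h. With a = (8.5 − μ)/SD, and φ and Φ the normal density and distribution function:

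rise = (1 − r) × SD × φ(a)/Φ(a)

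In minutes the multiplier is 0.3 × 0.7 × 60 = 12.6. The article does not give μ, so it is varied as an assumption.

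| μ (assumed) | a | φ(a)/Φ(a) | Rise with no effect | True rise that reaches 30 min |
|---|---|---|---|---|
| 8.0 h | 0.714 | 0.405 | 5.1 min | 24.9 min |
| 8.5 h | 0 | 0.798 | 10.1 min | 19.9 min |
| 9.0 h | −0.714 | 1.301 | 16.4 min | 13.6 min |

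**Sensitivity to r (assumed values).** For μ of 8.0 to 9.0 h the rise is 8.5 to 27.3 min at r 0.5 and 1.7 to 5.5 min at r 0.9. At the plan's r of 0.7 it is still only 19.9 min at μ 9.25 h. It exceeds 30 min only in a corner such as r 0.5 with μ 9.25 h (33.2 min), where 14% of screened children would qualify.

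**Calendar.** Take 26 intervention weeks and about 24 follow-up weeks, and assume a 10-week summer.
- Intervention: 10/26 = 38% of weeks, against 75% required (0.75 × 26 = 19.5 weeks).
- Follow-up: 10/24 = 42% of weeks, against 50% required (12 weeks).
- In a simulation with no intervention effect and an assumed 30 min of extra summer sleep, the group mean passed in exactly those shares of weeks (38% or 42%). That is below both limits.

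**If the rule were applied child by child.** In the same simulation, 3.6% to 8.7% of children met both limits with no effect and no summer gain, for μ of 8.0 to 9.0 h. With the assumed summer gain in the intervention phase, the range was 7% to 15%.

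**The case against.** The strongest reply is that components are already chosen on randomized contrasts (section 3.7.1). A rise shared by all 16 conditions cancels there, so no untreated arm is needed to choose between levels. This stands. A reader might infer that the Aim 1 factor tests are biased, and the document does not support that.

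A reader might also infer that every condition could pass on artefact alone. That is not supported either. At the plan's SD and r the rise stays well short of 30 min, and a 10-week summer meets neither week limit.

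The inputs are open to challenge. The screened mean is not given, and the result triples across the assumed range. The article says its parameters come from prior studies, not that they describe children before selection. It would also be wrong to enlarge the figures by taking the square root of Aim 3's error variance of 1.1 as a between-child SD, because section 3.6.3 does not define it that way.

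On summer, the document gives neither size nor direction. A child whose run-in falls in summer would be biased the other way. If recruitment were even over the year, baseline weeks would fall in summer as often as study weeks, and much of the shift would average out at group level. Fuller calendar rules may also exist in a document not shown.

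Finally, section 3.5.1.1 cites the prior research for feasibility and adds evidence of benefit, so the pilot contrast is not its only support. The evaluation trial would estimate the effect afresh. The cost is a mistaken decision to proceed, not a false effect claim.

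None of this changes what the mark measures: a raw rise from the value used for selection.

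**Conclusion.** The point holds for the absolute pass mark and only for that. Followed as written, the rule credits regression to the mean toward the 30 min. The amount is about 5 to 16 min at SD 0.7 h and r 0.7 for a screened mean of 8.0 to 9.0 h, so a true rise of about 14 to 25 min would suffice. The bar is lowered; a pass is not produced by selection alone.

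The size rests on four assumptions: a normal run-in mean, equal variances before and after, an SD and r that apply to children before selection, and a baseline mean identical to the selection mean. If the baseline uses only the weeknights of run-in week 2, the overlap is partial and the size would shift somewhat.

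The calendar part is weaker. The share of passing weeks depends on when summer falls, but the direction depends on whether the baseline or the later weeks fall in summer.

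**What to change.** - Keep component selection on the section 3.7.1 contrasts, and say in section 3.5.1.1 how the 30-min mark relates to them.
- State the mark in one of two ways. The first is a model-based difference from a named reference condition. Condition 1 in Table 1 is the natural choice, with a note that this measures added effect only, because that condition already has a goal, messages and tracker. The second is the model-predicted rise minus the expected regression to the mean.
- If the second is used, report a sensitivity range for r and for the screened-population mean. The week 1 to week 2 correlation in the run-in cannot settle r alone, since the article expects self-monitoring to alter sleep at first.
- Add a school-in-session term to the model and evaluate the 75% and 50% week criteria at in-session values.
- Report raw change from baseline as descriptive.

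The cost is analysis wording plus school calendar dates, with no new participants or visits. The downside is that the criterion becomes harder to meet.
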